#### School staff members’ knowledge and skills

Teachers’ knowledge, skills, and experience with P4C will be measured using the Educator Knowledge, Skill and Experience Questionnaire [27]. The questionnaire uses a five-point Likert scale from strongly disagree to strongly agree. The questionnaire has been translated into Swedish following a forward–backward translation process and previously used in Swedish elementary schools by teachers. Time frame: baseline, four months, and eleven months (both intervention and control classes).

OTs knowledge, skills, and experience of P4C will be measured using the Partnering for Change Occupational Therapist Questionnaire: Exploring Occupational Therapist Skills, Knowledge and Beliefs [27]. The questionnaire uses a five-point Likertscale from strongly disagree to strongly agree. The questionnaire has been translated into Swedish following a forward–backward translation process and has been complemented with questions relevant for the Swedish school system including questions on children with neurodevelopmental disorders. The questionnaire has been previously used in Swedish elementary schools by OTs. Time frame: baseline, four months, eleven months (for both intervention and control classes).

#### School staff members’ experience of working with P4C

Additionally, after the intervention study, focus group interviews will be conducted with school staff (OT, teacher, special education teacher and/or principal) (one focus group/school) to explore the experience of working according to P4C, and if any facilitators and barriers for implementation were identified. The interviews will be digitally recorded and transcribed verbatim.

#### Children’s’ experience of their learning environment

To describe children’s experiences of inclusive learning environments, focus group interviews will be conducted after P4C with six to eight children from intervention classes. The interviews will be digitally recorded and transcribed verbatim.

### Sample size

According to the effect size calculation for a two-sample t-test with alpha 0.05 and a power of 80% using the primary outcome (EEL), a total of 400 children should be recruited for the intervention study, 200 each in intervention and control classes, respectively (Stata v.17, StataCorp LLC, College Station, TX, USA). The calculation was based on a previous Swedish study using the EEL for sixth graders (email from [name], PhD, [contact], April 2023) reporting a mean score of 3.21 and an SD of 0.74. With the above-mentioned parameters, a difference of 0.21 units in the mean between the groups can be detected, using a p-value of < 0.05 with 80% power.

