### Study setting and eligibility criteria

The intervention study will be conducted in elementary schools that include classes from preschool to sixth grade. Inclusion criteria for intervention- and control classes are: (a) preschool class or primary school class (grades 1–6), (b) have a Pupil Health Team with special education competence, (c) there are children with unmet special educational needs as perceived by the school staff, and (d) the principal and class teacher both consent to participate in the intervention study. The intervention classes will have access to an OT working according to P4C. OTs working according to P4C must have attended an online training course. Approximately 400 children in total (intervention and control, allocation ratio 1:1) will participate in the study.

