### Statistical analysis

#### Effectiveness of P4C

Descriptive statistics will be presented for demographic characteristics and outcome variables. To evaluate any potential changes following the P4C, the difference-in-differences method using regression modelling will be applied [45]. This method compares the changes in outcomes over time between the intervention and control group and allows for adjustment for confounders. Furthermore, the multilevel structure of the design of the study will be considered. If the proportion of missing data is between 5% and 40%, multiple imputation will be performed [46]. Estimates will be reported with 95% confidence intervals and associated p-values. A two-tailed p-value of < 0.05 will be considered statistically significant.

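### The statement of 80% power for 0.21 EEL units comes from a t-test on independent children; a study that recruits and treats whole classes does not support it.

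*Protocol article*

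**What the plan says.** The Sample size section of the protocol article opens: "According to the effect size calculation for a two-sample t-test with alpha 0.05 and a power of 80"%. It concludes that "a total of 400 children should be recruited for the intervention study, 200 each in intervention and control classes, respectively". The input is an earlier Swedish study of sixth graders, "reporting a mean score of 3.21 and an SD of 0.74", and the result is that "a difference of 0.21 units in the mean between the groups can be detected, using a p-value of < 0.05 with 80% power". The section mentions no class size, number of classes, ICC, design effect, baseline–follow-up correlation or allowance for attrition. Study setting and eligibility criteria repeats the total: "Approximately 400 children in total (intervention and control, allocation ratio 1:1) will participate in the study".

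The same article describes a clustered study:
- Study setting and eligibility criteria defines eligibility for classes, with agreement from the principal and the class teacher.
- Recruitment has control classes matched to intervention classes.
- Intervention classes receiving P4C starts with measures for the entire class.
- Outcome measures has teachers score the EEL, the primary outcome.

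Under Statistical analysis, Effectiveness of P4C, the plan is a difference-in-differences regression, "the multilevel structure of the design of the study will be considered", and the test is two-sided: "A two-tailed p-value of < 0.05 will be considered statistically significant".

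**The concern.** The power statement and the analysis rest on different models. Children in one class share a teacher, a classroom and a programme, and their EEL scores may also share a rater. Their scores are then likely to be correlated, and 200 children per arm carry less information than 200 independent observations. The calculation is also a comparison at one time point, whereas the planned analysis compares changes from baseline. The first mismatch makes the stated figure too favourable. The second can make it too favourable or too unfavourable, depending on how strongly baseline and follow-up scores correlate.

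This is the only power claim for the primary outcome. If it stands, a null result could be read as evidence against an effect of 0.21 units, although the study may have had much less than 80% power to find one.

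**Working it through.** **Inputs from the article.** n = 200 per arm, SD 0.74, difference 0.21, two-sided alpha 0.05, power 80%.

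**Assumed, because the article gives none of them.** Class size m = 20 (10 classes per arm), an ICC range, and baseline–follow-up correlation ρ.

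**1. The stated figure.** SE = SD × √(2/n) = 0.74 × √(2/200) = 0.0740. Detectable difference = (1.960 + 0.842) × 0.0740 = 0.207; the exact t calculation gives 0.208. Power at 0.21 is 81.0% (normal) or 80.8% (t). Required n per arm = 2 × 0.74² × 2.802² / 0.21² = 194.9, so 195 (196 by exact t). The article's arithmetic is right for independent children.

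**2. How much clustering that figure tolerates.** The design effect is DE = 1 + (m − 1) × ICC. The margin is 200 / 194.9 = 1.026. At m = 20, ICC = 0.026 / 19 ≈ 0.0014. At m = 10, ICC = 0.026 / 9 ≈ 0.003. Beyond that, the stated test falls below 80%.

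**3. The stated post-only test with clustering, m = 20.** SE = 0.74 × √(2/200 × DE). The first figure of each pair uses the normal approximation, the second a t distribution with 20 − 2 = 18 df. Detectable difference = 2.80 × SE or 2.96 × SE.

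| ICC | DE | SE | Power at 0.21 | Detectable at 80% |
|---|---|---|---|---|
| 0.02 | 1.38 | 0.087 | 67.6% / 62.8% | 0.24 / 0.26 |
| 0.05 | 1.95 | 0.103 | 52.9% / 48.5% | 0.29 / 0.31 |
| 0.10 | 2.90 | 0.126 | 38.5% / 35.1% | 0.35 / 0.37 |

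**4. Difference-in-differences, m = 20.** SD of change = 0.74 × √(2(1 − ρ)). At ρ = 0.7 this is 0.573, and the ICC is now that of the change score.

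| ICC of change | SE | Power at 0.21 | Detectable at 80% |
|---|---|---|---|
| 0.02 | 0.067 | 87.7% / 83.9% | 0.19 / 0.20 |
| 0.05 | 0.080 | 74.7% / 69.9% | 0.22 / 0.24 |
| 0.10 | 0.098 | 57.6% / 53.0% | 0.27 / 0.29 |

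At ρ = 0.5 the SD of change is 0.74 × √1 = 0.74, so the results equal those in step 3 for the same ICC: nothing is gained over the post-only test.

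**5. Sensitivity to class size and correlation.** With m = 10 (38 df), ρ = 0.7 and ICC of change 0.05, power is 86% / 84%. With m = 20, ρ = 0.8 and ICC of change 0.05, it is 89.5% / 85.9%. With m = 10 and ICC 0.05, the post-only test has 65% / 63%.

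**The case against.** The strongest reply is that step 3 describes a test the study will not run. The planned analysis uses baseline EEL. Where the same teacher scores a class both times, stable leniency or severity cancels in the change, so the ICC of change may be much smaller than the ICC at one time point. The article also reports good test–retest reliability for the EEL. Steps 4 and 5 show power above 80% in settings that are not extreme. This stands, and it rules out saying that the study lacks 80% power. It does not rescue the statement as written, because the Sample size section assumes no correlation and takes no credit for baseline scores.

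A second reply is that the Statistical analysis section already allows for the multilevel structure and that further detail may sit in a fuller document. That is fair for the model specification, and the choice of random effects or degrees of freedom is no part of this point. But the article itself prints a power claim, and that claim reproduces only with no clustering. A later analysis model can give correct standard errors; it cannot make 0.21 at 80% follow from independent children.

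A reader might also infer four stronger things that the article does not support:
- **That up to 40% missing data is expected.** The 5% to 40% range only sets when multiple imputation applies; it is not a forecast.
- **That the study has some 16 to 20 classes.** This follows only from assuming 20 to 25 children per class; no count is given.
- **That the false-positive rate is inflated.** That would require an analysis ignoring class, and the plan says otherwise.
- **That 0.21 is a clinically important target.** It is presented only as a detectable difference, and the planned 95% confidence intervals will show the precision achieved if clustering is modelled.

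**Conclusion.** The point holds in a limited form. The statement of 80% power for 0.21 EEL units is not supported by the design. For the test it names, it is true only if the ICC is essentially zero (about 0.001 at 20 per class).

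For the planned analysis, power cannot be determined from the article. At 20 per class and correlation 0.7 it runs from above 80% to little more than 50% as the ICC of change goes from 0.02 to 0.10, and it is lower at correlation 0.5. It is tempting to conclude that the promised power is not delivered. The article does not allow that, because ICC, class size and correlation are all unstated and plausible combinations fall on both sides of 80%. What can be said is that power may be well below the stated level and that the calculation shown gives no assurance otherwise.

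**What to change.** Keep the target of 400 children and replace the 0.21/80% sentence with the difference detectable by the planned clustered difference-in-differences analysis. State with it:
- the expected number and size of classes;
- an ICC range;
- the assumed baseline–follow-up correlation;
- an allowance for attrition.

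If these cannot be given, the minimum change is to label 0.21 as the difference detectable when children are independent, without clustering.

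The cost is wording in one section and no additional children. The stated detectable difference may become less favourable. The change corrects the claim; it does not by itself add power.

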### Outcome measures

Data collection will occur at: (i) baseline, prior to the intervention (T1); (ii) immediately following the intervention (T2); and (iii) eleven months follow-up post-baseline (T3). An overview of all outcome measures and data collection points is presented in Table 2.

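### The 80% power for a 0.21-unit EEL difference is stated for children recruited, but on its own t-test basis it needs about 98% of them to have analysable scores

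*Protocol article*

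**What the plan says.** The Sample size section sizes the study with a two-sample t-test on the primary outcome, the teacher-rated EEL, at alpha 0.05 and 80% power. The variability comes from an earlier Swedish study of sixth graders, "reporting a mean score of 3.21 and an SD of 0.74". The section states that "a total of 400 children should be recruited for the intervention study, 200 each in intervention and control classes, respectively" and concludes that "a difference of 0.21 units in the mean between the groups can be detected, using a p-value of < 0.05 with 80% power". Study setting and eligibility criteria repeats the number: "Approximately 400 children in total (intervention and control, allocation ratio 1:1) will participate in the study".

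Under Outcome measures, the EEL is collected at baseline, at four months and at eleven months after baseline, in both intervention and control classes. Under Effectiveness of P4C, the planned analysis is a difference-in-differences regression that takes the multilevel structure into account. That section adds: "If the proportion of missing data is between 5% and 40%, multiple imputation will be performed". The article gives no expected rate of loss or of missing EEL scores.

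**The concern.** The same 200 per arm serves both as the recruitment target and as the number behind the detectable difference. That is harmless only if almost every recruited child contributes an analysable EEL score. A change from baseline needs a score at baseline and another at four or eleven months. Some loss is plausible from the design. The intervention lasts one semester, the last score comes eleven months after baseline, the participating schools end at sixth grade, and participants may withdraw at any time.

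The power claim carries no condition. If a material share of scores is missing, 80% power for 0.21 may not apply to the data analysed, and 0.21 would be smaller than the difference the study could reliably detect. An inconclusive primary result, particularly at eleven months, could then be given more weight against a 0.21-unit effect than it deserves. A later analysis plan cannot change how many children were recruited, so the printed figure should say what it rests on.

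**Working it through.** **Inputs.** SD 0.74, difference 0.21, 80% power and 200 per arm, from Sample size. Two-sided alpha 0.05: Effectiveness of P4C states "A two-tailed p-value of < 0.05 will be considered statistically significant". Children are treated as independent, as the stated t-test does.

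**Step 1: reproduce the plan's figure.**

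- Number needed per arm (normal approximation): n = 2 × (1.960 + 0.842)² × 0.74² / 0.21² = 2 × 7.849 × 0.5476 / 0.0441 ≈ 194.9, so 195. The exact t-test gives 195.9, so 196.
- Detectable difference with 200 per arm: (1.960 + 0.842) × 0.74 × √(2/200) = 0.207. The exact t-test gives 0.208. Both round to the printed 0.21.
- Power for 0.21 with 200 per arm: 0.810 (normal), 0.808 (t-test).

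The arithmetic is correct for 200 analysed per arm. The slack is 200 − 196 = 4 children per arm, or 4/200 = 2%. In total, 392 of the 400 must be analysable.

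**Step 2: effect of missing scores, complete cases only.** Analysed number per arm = 200 × (1 − d), where d is the proportion lost. The article gives no d. The values below are assumptions, spanning the range named in the imputation rule. Power and detectable difference are from the exact t-test.

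| Loss d | Analysed per arm | Power for 0.21 | Detectable difference at 80% power |
|---|---|---|---|
| 0% | 200 | 0.808 | 0.208 |
| 5% | 190 | 0.788 | 0.213 |
| 10% | 180 | 0.766 | 0.219 |
| 20% | 160 | 0.716 | 0.232 |
| 30% | 140 | 0.658 | 0.249 |
| 40% | 120 | 0.591 | 0.269 |

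At 5% loss the shortfall from 80% is about 1 point and the detectable difference still rounds to 0.21. At 20% the shortfall is about 8 points, and at 40% about 21.

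**Step 3: what the planned analysis could change.** With equal SDs at the two times and pre-post correlation r, a change score has SD 0.74 × √(2(1 − r)). The article does not give r, so these values are also assumptions.

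- r = 0.5: SD = 0.74 × √1.0 = 0.74. The t-test figures apply unchanged.
- r = 0.6: SD = 0.74 × √0.8 = 0.662. Power is about 0.81 at 20% loss and 0.69 at 40%.
- r = 0.7: SD = 0.74 × √0.6 = 0.573. Power is about 0.81 even at 40% loss.
- r = 0.4: SD = 0.74 × √1.2 = 0.811. With no loss at all, 0.21 / (0.811 × √(2/200)) = 2.59, and 2.59 − 1.96 = 0.63, which gives power of about 0.74.

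In general, loss is exactly offset when 2(1 − r) = 1 − d, that is, when d = 2r − 1. Multiple imputation is not modelled here. It could recover part of the lost information.

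**The case against.** The strongest reply is that nothing in the Sample size section is miscalculated and that the imputation rule is a contingency, not a prediction. That is right. A reader might infer that the plan expects 5–40% loss, or that the two sections contradict each other. The text supports neither reading: the rule is conditional, refers to missing data in general rather than to EEL scores, and can stand beside a calculation on 200 per arm. It is likewise too strong to say that the trial lacks 80% power unless nobody is lost. About 392 complete children suffice, and at 5% loss the difference is negligible.

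The loss figures also rest on a complete-case t-test at one time point, whereas the plan is difference-in-differences with imputation. A child missing one follow-up may have a baseline score and the other follow-up score for the imputation to use. With a correlation of 0.6 or 0.7, sizeable loss would be absorbed. So an actual shortfall cannot be established from the article. Further, the EEL is completed by teachers, so loss may be well short of 40%, and reporting 95% confidence intervals limits the risk of over-reading a null result.

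What these points do not answer is that the printed claim invokes neither imputation nor a favourable correlation. It rests on a t-test with about 2% slack and is stated without condition for a number recruited.

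**Conclusion.** The point holds in a limited form. The figure of 80% power for 0.21 units is correct for about 196–200 analysed children per arm but is presented as a property of 200 recruited per arm, with no stated allowance for missing EEL scores over eleven months.

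The consequence is conditional and its size is unknown. On the article's own t-test basis, with independent children and complete cases, it is trivial at 5% loss, moderate at 20% (power about 72%, detectable difference about 0.23) and substantial at 40% (about 59% and 0.27). The direction is that power would be overstated and the detectable difference understated. A pre-post correlation above 0.5, or effective imputation, would reduce or remove the shortfall; a correlation below 0.5 would deepen it. Clustering of children in classes is a separate matter and is left out of all these figures.

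**What to change.** Keep recruitment at 400 and restate the Sample size section:

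- Say that 0.21 units at 80% power applies to about 196–200 analysed children per arm.
- State an assumed completeness of EEL scores at four and at eleven months, and give the detectable difference (or the power for 0.21) for each. On the present t-test basis, 20% loss would give about 0.23 units, or about 72% power.
- Base these figures on the planned difference-in-differences analysis and state the pre-post correlation assumed. If the sponsor relies on that correlation or on imputation to make up for losses, the section should say so.

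The cost is a few sentences and a short recalculation, with no additional children. The only downside is that the stated figure may look less favourable.

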### Data management

A data management plan (DMP) will be developed by the principal investigator in accordance with the Swedish National Data Service (SND). All data will be monitored regularly, entirely independently from sponsors and competing interests. Each child will be coded by school staff, and the code key connecting names to numbers will be kept in a separate, secure location at each school. All data will be securely stored on a platform for research data at Uppsala University. Access will be password protected, and only the principal investigator and co-researchers will have access to the final dataset.

### Statistical analysis

#### Effectiveness of P4C

Descriptive statistics will be presented for demographic characteristics and outcome variables. To evaluate any potential changes following the P4C, the difference-in-differences method using regression modelling will be applied [45]. This method compares the changes in outcomes over time between the intervention and control group and allows for adjustment for confounders. Furthermore, the multilevel structure of the design of the study will be considered. If the proportion of missing data is between 5% and 40%, multiple imputation will be performed [46]. Estimates will be reported with 95% confidence intervals and associated p-values. A two-tailed p-value of < 0.05 will be considered statistically significant.

#### Health economic evaluation

Cost-effectiveness analyses will be conducted as a within-trial economic evaluation comparing the health outcomes, school attendance, and societal costs between the intervention and control classes. We plan to conduct a cost-utility analysis (CUA) and cost-effectiveness analysis (CEA), which focus on the health outcomes produced, while the total society costs are related to health gains and the result is expressed as an incremental cost effectiveness ratio (ICER). The primary health outcome in economic evaluation is defined as quality adjusted life years (QALYs) gained and will be estimated using any change in utilities, measured by CHU9D instrument at baseline and respective data collection points. The change in QALYs will be estimated by multiplying the change in estimated utilities with the intervention period expressed in years. The reduction in absenteeism rate will be used as a secondary health outcome and collected during the follow-up period as well as the consumption of additional support and healthcare at school. Costs to deliver P4C will be estimated based on professionals’ time needed to deliver the intervention at school, costs of materials, and other related costs. Other societal costs such as additional support materials/equipment at school will be estimated on the group level. The total societal costs will be estimated for intervention and control classes. The cost–utility ratio will estimate the price for one additional QALY—i.e., one life year with full health gained—while the cost–effectiveness ratio will calculate the price for an avoided case of absenteeism comparing intervention and control classes. The total QALY-gain for the children during the follow-up period will be estimated using the ‘area under the curve’ method [47]. QALYs will be analysed with general regression model (GLM) [48], which allows for the control of confounders and adjustments to baseline. The costs and potential savings will be related to health gains and reduction on absenteeism, and then presented as cost–effectiveness ratios on a cost–effectiveness plane, together with uncertainty for cost- and effect data. Probability for P4C to be cost-effective compared with TAU will be presented as a range of ‘willingness-to-pay’, representing the intentions of decision-makers to pay for an additional QALY or for reduction of certain percent in absenteeism, using a ‘cost–effectiveness acceptability curve’ (CEA) [49], and bootstrap regression analysis.

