**Methods:**

In a parallel, non-randomised controlled intervention design, 400 children, aged 6–12 years, and their teachers, will be recruited to either intervention classes, working according to the P4C, or to control classes (allocation ratio 1:1). Data will be collected at baseline, post-intervention (4 months), and 11 months follow-up post baseline. The primary outcome is children’s engagement with learning in school. Secondary outcomes include for example children’s health-related quality of life and wellbeing, occupational performance in school, attendance, and special educational needs. The difference-in-differences method using regression modelling will be applied to evaluate any potential changes following P4C. Focus group interviews focusing on children, and professionals’ experiences will be performed after P4C. A health economic evaluation of P4C will be performed, both in the short term (post intervention) and the long term (11-month follow-up). This study will provide knowledge about the effectiveness of P4C on children’s engagement with learning, mental health, and wellbeing, when creating inclusive learning environments using a combination of class-, group- and individual-level interventions.

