## Methods: participants, interventions, and outcomes

### Study design

The study will be conducted as a parallel, non-randomised controlled intervention study, with pre-, post- and 11-month follow-ups. It will include a qualitative evaluation involving interviews with school staff and children after P4C. The study will be conducted in elementary schools in Sweden during one school semester (approximately four months). In Swedish elementary schools, all pupils have access to Pupil Health Teams (PHTs), which will constitute treatment as usual (TAU). Intervention classes will also work according to P4C. Study design and enrolment details are presented in Fig. 1. This protocol is reported in accordance with the Standard Protocol Items: Recommendations for Interventional Trials (SPIRIT) [30] (Supplemental files 1). The intervention study has been approved by the Swedish Ethical Review Authority (2023-00013-02, 2021-06412-02, 2019-03954), and registered as a clinical trial at ClinicalTrials.gov (NCT05435937).

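### QALYs gained are defined by two rules that do not agree, and the product rule overstates the short-term gain up to twofold if utility changes steadily or early

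*Protocol article*

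**What the plan says.** All of this stands in the protocol article, mainly under *Health economic evaluation*.

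- Status of the outcome: "The primary health outcome in economic evaluation is defined as quality adjusted life years (QALYs) gained".
- Source of the utilities: "estimated using any change in utilities, measured by CHU9D instrument at baseline and respective data collection points".
- First rule: "The change in QALYs will be estimated by multiplying the change in estimated utilities with the intervention period expressed in years".
- Second rule, further down the same section: "The total QALY-gain for the children during the follow-up period will be estimated using the ‘area under the curve’ method". QALYs are then to be analysed with a GLM that allows adjustment for confounders and for baseline.
- Timing, from the Abstract: "Data will be collected at baseline, post-intervention (4 months), and 11 months follow-up post baseline". *Outcome measures* gives the same three time points for CHU9D in both groups.
- Length of the intervention: *Study design* puts it at one semester, about four months.
- Horizons: the Abstract announces an economic evaluation both after the intervention and at the 11-month follow-up.

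**The concern.** Multiplying a utility change by the length of the intervention treats the whole change as present from the first day and counts nothing after the intervention ends. An area under the curve lets the change build up between measurements and runs to the last measurement used. Applied to the same CHU9D data, the two rules generally give different QALYs.

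The QALY difference is the denominator of the cost-utility ratio and drives the acceptability curve for QALYs. Cost-effectiveness is part of the study aim and is a research question of its own. With two rules in the plan, the choice between them could be made after the results are known, and in a non-randomised study prespecification is an important safeguard.

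**Working it through.** The protocol states no QALY figure, so there is none to reproduce. The check compares the two rules on the protocol's own schedule.

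**Inputs**
- Intervention period: about 4 months = 4/12 = 0.333 year (*Study design*).
- CHU9D at T1 = 0, T2 = 4 months and T3 = 11 months, so the segments are 4/12 and 7/12 year (Abstract; *Outcome measures*).
- d2 and d3: differences between groups in utility change from baseline at T2 and T3.
- Assumption: straight lines between measurements (trapezoidal area). The protocol names the area method but not the interpolation.

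**Short term, T1 to T2**
- Product rule: d2 × 4/12 = 0.333 d2.
- Trapezoidal area: ½ × d2 × 4/12 = 0.167 d2.
- Ratio: 0.333 / 0.167 = 2.

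The factor of 2 is exact for linear change. If utility moved fully at baseline, the true area would be 0.333 d2 and the product rule would be right. Change that comes early in the semester lies between 1 and 2. Change concentrated late would put the factor above 2. With two measurements, the path between them is not observed. At a fixed incremental cost C, the cost per QALY is C / (0.333 d2) instead of C / (0.167 d2), which is half.

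**Eleven months, T1 to T3**
- Trapezoidal area: ½ × d2 × 4/12 + ½ × (d2 + d3) × 7/12 = 0.458 d2 + 0.292 d3.
- Product rule, if it were applied here: 0.333 × the utility change. The text does not say whether that is the change at T2 or at T3, so both are shown.

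| Trajectory | Area | Product, T3 change | Product, T2 change |
|---|---|---|---|
| d3 = d2 = d (sustained) | 0.750 d | 0.333 d (44%) | 0.333 d (44%) |
| d3 = ½ d2 | 0.604 d2 | 0.167 d2 (28%) | 0.333 d2 (55%) |
| d3 = 0 | 0.458 d2 | 0 (0%) | 0.333 d2 (73%) |
| d2 = ½ d3 | 0.521 d3 | 0.333 d3 (64%) | 0.167 d3 (32%) |
| d2 = 0 (late only) | 0.292 d3 | 0.333 d3 (114%) | 0 (0%) |

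Percentages are product over area. For a sustained effect, the cost per QALY at fixed incremental cost would be 0.750 / 0.333 = 2.25 times as high under the product rule. With the T3 change the direction reverses when nearly all the effect appears after T2: 0.333 d3 = 0.458 d2 + 0.292 d3 gives d3 = 11 d2 as the break-even.

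**A looser meaning of the period.** If the intervention period were meant as the full 11 months, the product would be 11/12 × d = 0.917 d against 0.750 d for a sustained effect, a ratio of 1.22. The two rules would still disagree.

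**The case against.** The strongest reply is that the sentences need not compete. The product sentence follows directly on the definition of QALYs gained and can be read as a loose statement of principle (utility times time), with the area under the curve as the operational method. Or the two terms, intervention period and follow-up period, may mark the two announced horizons, with the product for the short term and the area for 11 months. The article is also condensed, and detailed QALY computation is often left to a fuller economic plan.

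Part of this stands. A reader might infer that the plan cuts the 11-month gain off at month 4, or that the two horizons are wrong by about a factor of two in opposite directions. The documents do not support either as a general statement. For the follow-up period the text names the area method, so the truncation arises only if the product rule is carried to that horizon. Its size and direction then depend on the trajectory and on which change is multiplied.

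The rest does not stand. No sentence assigns a rule to a horizon, and the utilities are tied to all the data collection points. Splitting the rules by horizon removes the truncation but leaves the short-term overstatement, and the two horizons would then use different definitions of a QALY. Nor is this an omitted detail: the article states one formula and then a different method.

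**Conclusion.** The inconsistency is real: there are two current rules for the primary economic outcome and no statement of which governs. The firm numerical consequence is in the short-term analysis, where the product rule gives twice the trapezoidal QALY gain. That factor rests on linear change between T1 and T2. It shrinks to none for an immediate change. The halving of cost per QALY further assumes a fixed incremental cost.

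The 11-month effect is conditional. It exists only if the product rule is used there, and the 0.333d against 0.750d comparison applies only to an effect sustained from T2 to T3.

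The reach is limited to the cost-utility results. The EEL analysis, the sample size and the absenteeism ratio do not depend on it.

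**What to change.** Delete the product sentence and state one rule for both horizons: each child's QALYs are the trapezoidal area under the CHU9D utility curve.

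- Short term: T1 and T2, one segment of 4/12 year.
- Eleven months: T1, T2 and T3, segments of 4/12 and 7/12 year.
- Estimate the difference between groups in the GLM already planned, adjusted for baseline CHU9D utility.

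The cost is one sentence removed and one reworded. CHU9D is already scheduled at all three times in both groups, so no new data are needed. The change should be made before the economic analysis begins.
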